**Review of existing knowledge related to proposed research proposal**

*Hepatitis C virus (HCV)*

Hepatitis C (HCV) virus is a hepatotropic virus wwhich infects and multiply in hepatocytes. A large proportion of those who acquires HCV infection, fails to clear the virus naturally and progress to develop chronic hepatitis C (CHC) (3). Unchecked CHC, in a sizeable proportion, may progress to liver cirrhosis and hepatocellular carcinoma (4, 5), both of which are potentially-fatal conditions. All those with CHC shall be treated to clear the virus.

*Burden of HCV infections – worldwide*

World Health Organization’s (WHO) global estimates, viral hepatitis caused 1.34 million deaths in 2015. This number is comparable to deaths caused by tuberculosis and higher than those caused by HIV. Most of the viral hepatitis related deaths in 2015 were due to chronic liver disease (720,000 deaths due to cirrhosis) and primary liver cancer (470,000 deaths due to hepatocellular carcinoma). Globally, in 2015, an estimated 71 million people were living with chronic HCV infection (6) and it accounted for approximately 399,000 annual deaths.

*Global target of HCV elimination*

Considering the huge burden of HCV and its associated morbidity/mortality, the World Health Assembly in May 2016 endorsed the Global Health Sector Strategy (GHSS) for 2016–2021 on viral hepatitis (HBV and HCV infection), which proposes to eliminate viral hepatitis as a public health threat by 2030. The elimination is defined as reduction, as compared to baseline in 2015, in new infections (incidence) by 90% and viral hepatitis related deaths (mortality) by 65% by the year 2030.

To achieve the WHO target, the government of India has recently launched public funded “National Viral Hepatitis Control Program (NVHCP)”.

*HCV treatment*

HCV infection is treated with a group of drugs called as Direct Acting Antiviral agents (DAAs). These DAAs are orally administered and are highly safe and effective. The effectiveness of these drugs is slightly low in patients with cirrhosis. In absence of cirrhosis, these DAAs successfully clears the virus in ~95% of those who have taken the complete course of treatment (7).

DAAs based regimen are effective against either certain genotypes (genotype specific regimen) or all genotypes (pangenotypic regimen). Use of genotype specific regimen need genotyping of the virus circulating in a given patient before start of DAA. HCV genotyping is a costly investigation which need time, trained manpower, and specific instruments. Hence, across the globe, pangenotypic treatment are preferred over genotypic specific regimens. At least six genotypes are known for HCV, namely HCV genotypes 1-6. In India, the HCV genotype 3 and 1 are the most common and account for more than 95% of HCV infection (8).

Several genotypic specific and pangenotypic DAAs based treatment regimens are approved for the treatment of non-cirrhotic patients with genotype 3 or genotype 1 HCV infection. Among them, only few are available in India (Table 1) (9).

**Table 1: Treatment regimens available in India**

| **No** | **Type** | **Genotypes against which it is effective** | **Drugs** | **Duration** |
| --- | --- | --- | --- | --- |
| 1 | Genotype specific | Genotype 1, 4, 5, 6 | Sofosbuvir plus Ledipasvir | 12 weeks |
| 2 | Genotype specific | Genotype 3 | Sofosbuvir plus Daclatasvir | 12 weeks |
| 3 | Pangenotypic | All genotypes | Sofosbuvir plus Velpatasvir | 12 weeks |

*Comparison of 8 weeks versus 12 weeks of HCV treatment*

One of the major bottle-neck in successful HCV treatment is “12 weeks duration” of treatment. Long-duration of treatment poses logistic issues of maintaining the drug supply, poor drug compliance, and increased cost of therapy. Hence, efforts are done to reduce the treatment duration without compromising its effectiveness. Several studies, for the regimens which are available in India, have shown that the 8 weeks of treatment duration are comparable to usual 12 weeks of therapy (Table 2).

**Table 2: Data on comparison of 8 weeks versus 12 weeks of treatment regimens (available in India) in non-cirrhotic patients with HCV infection**

| **No** | **Author, year** | **Patient characteristics** | **Study design** | **DAA Combination used** | **Virological response as SVR12 (%)** | |
| --- | --- | --- | --- | --- | --- | --- |
| **8 weeks** | **12 weeks** |
| 1 | Kowdley et al, 2014 (ION-3) (10) | Non-cirrhotic, Genotype 1, treatment naive | Open-label, RCT | Sofosbuvir plus Ledipasvir | 94 | 95 |
| 2 | Marcus et al, 2018 (11) | Non-cirrhotic, Genotype 1, treatment naive | Open-label, RCT | Sofosbuvir plus Ledipasvir | 96.3 | 96.3 |
| 3 | Shiha et al, 2019 (12) | Non-cirrhotic, Genotype 4, treatment naive | Open-label, RCT | Sofosbuvir plus Ledipasvir | 95 | 98 |
| 4 | Yanny et al, 2018 (13) | Geriatric population, non-cirrhotic, genotype 1 | Retrospective study | Sofosbuvir plus Ledipasvir | 93 | 95 |
| 5 | Boyle et al, 2020 (14) | F2 or F3 fibrosis, Genotype 3, Treatment naive | Single arm (8 weeks duration), Observational study | Sofosbuvir plus Velpatasvir | 100  (per protocol analysis) | |
| 5 | Fu et al, 2021 (15) | Adolescent and children with HCV infection | Systematic review of 36 studies | Various combination | 100 | 98.8 |

*HCV burden in India*

Recently, our group conducted a systematic review of all the published literature on prevalence of HCV infection in India (16). This document from the basis of disease burden estimation for the “National Viral Hepatitis Control Program (NVHCP)” of India. In this review, we extracted data from 422 data points included in 355 studies. Among low-risk group population, we found that the anti-HCV seroprevalence in the country was anti-HCV seroprevalence rates was 0.85% (95% CI: 0.00%-3.98%) in community-based studies and 0.44% (0.40-0.49) in blood donors.

These data suggest that anti-HCV antibody prevalence in the Indian population is likely to be between 0.4% and 1.0%. Applying this to current population of India of around 1.30 billion, the number of anti-HCV positive persons in the country is thus likely to be between 5.2 and 13 million. With the prevalence of viremia among anti-HCV seropositive persons of 60%-70%, the number of persons with active HCV infection in the country should be in the range of ~3.0 to 9.0 million (16).

This systematic review is recently updated by our group to extract more accurate and updated information on HCV seroprevalence in the country (Unpublished report).

*Cost-effectiveness of HCV treatment in India*

Our previous work on mathematical modelling has shown that the treatment of HCV at a wider scale will be cost-effective as well as cost saving (17). This work supported the Government of India in planning the NVHCP. Our previous work had shown that the use of sofosbuvir/velpatasvir available at the current cost in the country is equal to sofosbuvir/daclatasvir (18). The cost-effectiveness will further be increased if the treatment duration could be reduced from 12 weeks to 8 weeks.

*National Viral Hepatitis Control Program (NVHCP) of India*

Government of India has launched a public funded, nationwide NVHCP. Though the program aims at prevention and control of all the viral hepatitis (Hepatitis A, Hepatitis B, Hepatitis C, and Hepatitis E) but as of now it is focussing on control and treatment of HCV. The national guidelines for the laboratory testing, diagnosis, and treatment are already in place and the treatment has been started in a few centres.

**Research gap:**

- Whether the duration of HCV treatment can be reduced without compromising the efficacy?

**Hypothesis**

Treatment with eight weeks of sofosbuvir-velpatasvir combination will not be inferior to that with twelve weeks in non-cirrhotic patients with chronic HCV infection.

**Objective of the study**

*Primary objective*

To compare the sustained virological response at week 12 (SVR12) after stopping 8 weeks or 12 weeks of sofosbuvir/velpatasvir in non-cirrhotic patients with chronic hepatitis C virus infection

*Secondary objective*

To compare the proportion of participants completing their planned 8 weeks or 12 weeks of treatment

*Relevance of proposed research project to public health*

If the 8 weeks treatment is proven to be non-inferior to usual 12 weeks treatment, then a shorter treatment duration can be widely implemented in national viral hepatitis control program. A shorter course of treatment is likely to have the following benefits

- Use of a single drug combination, instead of two different drugs, will ease the implementation of NVHCP in the most remote areas of the country without increasing the cost of treatment.
- Reduced treatment duration is likely to enhance the patients’ compliance to the drug treatment
- Enhanced compliance will culminate in reduced risk for drug default and drug resistance
- The results of this study could also be applied to several other Asian countries where the disease burden is high and the drug availability are similar to that in India.

*Relative importance of proposed research project in a given area (100 words)*

World Health Organization (WHO) has set the global target to eliminate the HCV by the year 2030 (1). The HCV elimination can be achieved through focus on prevention of new infection and treatment of infected persons. To achieve this target, India has recently launched a nationwide, public funded “National Viral Hepatitis Control Program (NVHCP)”.

In present era, HCV is treated with oral drugs which are safe and highly effective. Several treatment regimens are approved for HCV treatment. All the DAA regimes, which are available in India, has to be given for 12 weeks.

One of the major bottle-neck in successful HCV treatment is “12 weeks duration” of treatment. Long-duration of treatment poses logistic issues of maintaining the uninterrupted drug supply by the treatment provider and poor drug compliance by the patient. Hence, efforts are done to reduce the treatment duration without compromising its effectiveness.

*Applicability of your research project*

*(a) Short term*

HCV infected patients could effectively be treated with a shorter course of drugs.

*(b) Long term*

The results of this study and cost-effectiveness analysis are likely to lay down better policies as a part of the National Viral Hepatitis Control Program (NVHCP) of India, and thus should have a long-term, country-wide application. If the treatment duration could be reduced it will save money, improve the drug compliance, and increase the chance for the success of HCV elimination through NVHCP in the country.

**Preliminary work already done by the Investigator on this problem, e.g. selection of subjects, standardization of methods, with results, if any.**

We have treated a group of 27 dialysis dependent patients with acute hepatitis C virus infection. They were treated, regardless of their HCV genotype, with half daily dose of sofosbuvir plus daclatasvir for 8 weeks. The sustained virological response at 12 weeks (SVR12) on per protocol analysis was 96%. The manuscript has been published in a journal of Impact factor 6.0. The results of this study indicate that a shorter 8-week course of anti-HCV drugs may be as effective as the usual 12 weeks course.

***Goel A****, Bhadauria DS, Kaul A, Verma A, Tiwari P, Rungta S, Rai P, Gupta A, Aggarwal R. Acute hepatitis C treatment in advanced renal failure using 8 weeks of pan-genotypic daclatasvir and reduced-dose sofosbuvir. Nephrol Dial Transplant. 2020 Oct 23*

**Detailed research plan:**

*Methodology*

*Study design:* Multicentric, Open label, Randomized, Non-inferiority trial

*Study centres:*

1. Department of Gastroenterology, Sanjay Gandhi Postgraduate Institute of Medical Sciences, Lucknow (PI)
2. Department of Gastroenterology, King George’s Medical University, Lucknow
3. Department of Gastroenterology, Institute of Medical Sciences, Banaras Hindu University, Varanasi
4. Department of Gastroenterology, All Indian Institute of Medical Sciences, New Delhi
5. Department of Gastroenterology, GB Pant Hospital, New Delhi

*Study duration:* Three years: July 2022-June 2025

*Participant selection:* Participants who are attending the outpatient services in either of the participating institutes will be prospectively enrolled.

*Sequence generation:* central sequence generation will be done at PI’s institute (SGPGI) and the participants in either of the five institute will be sequentially allocated to the study arms. All the five centres will be coordinated by trial coordinate through WhatsApp or other similar medium.

*Randomization:* Computer generated sequence, Block randomization, block size of 4, 6 or 8, 1:1 ratio of allocation in two arms.

*Screening criteria*

All adults with active HCV infection will be screened for selection criteria

*Inclusion criteria*

1. Age >18 years
2. HCV mono-infection
3. Detectable HCV RNA (>10,000 IU/mL) in serum
4. Chronic HCV infection
5. No evidence of cirrhosis based upon a combination of history, examination, ultrasound, Transient elastography, APRI, FIB-4, Upper GI endoscopy

Exclusion criteria

1. Presence of cirrhosis
2. HBsAg or HIV coinfection
3. Estimated GFR <30 ml/ minute
4. Prior exposure to oral anti-HCV drugs, i.e, DAAs
5. Hepatocellular carcinoma or any other malignancy
6. Portal vein thrombosis
7. High-risk population such as people living with HIV, people on maintenance hemodialysis, thalassaemic or haemophiliacs, people who inject drugs, men have sex with men, high risk sexual behaviour

*Cirrhosis*

Cirrhosis will be defined as summarized in Figure 1 (given below)

[figure not shown]

**Flow of the participants**

[figure not shown]

*Sample size:*

We assumed the virological response in the reference group (12 weeks) is 95% and in the experiment group (8 weeks) as 90%, with a non-inferiority margin  of 5%, power 90% and level of significance 2.5%, with a one tailed alternative hypothesis. The required sample size is estimated as 400 participants in each arm. Assuming a 10% loss  to follow up, we raised the estimated sample size to 440 participants in each arm and total study size of 880.

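### The sample size assumes a true loss (95% versus 90%) equal to the 5% margin, so the stated inputs give 2.5% power, not 90%; 400 per arm matches 95% in both arms

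*Protocol*

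**What the plan says.** The hypothesis is one of non-inferiority: "Treatment with eight weeks of sofosbuvir-velpatasvir combination will not be inferior to that with twelve weeks" (Protocol, Hypothesis). The Sample size paragraph, under Flow of the participants, sets the rates: "We assumed the virological response in the reference group (12 weeks) is 95% and in the experiment group (8 weeks) as 90" per cent. It then gives a non-inferiority margin "of 5%, power 90% and level of significance 2.5%, with a one tailed alternative hypothesis". From these it concludes: "The required sample size is estimated as 400 participants in each arm". A 10% allowance for loss to follow-up raises this to 440 per arm, 880 in total. Allocation is 1:1 (Detailed research plan, Randomization). Nowhere else does the protocol give a different expected 8-week response or a different margin for the calculation.

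**The concern.** In a non-inferiority calculation, the expected rates must lie inside the margin; the distance between the expected difference and the margin is what the trial is powered to detect. Here the expected difference is 95% − 90% = 5 points and the margin is 5 points, so that distance is zero. The stated assumption is the boundary of the null hypothesis, not an alternative to it.

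Two things are at stake. First, a funder, ethics committee or later reader is told that the trial has a 90% chance of success if 8 weeks clears the virus in 90% of patients. On the protocol's own numbers it has almost none. Second, the text leaves open whether 90% is the response the investigators expect or the lowest they would accept. On the former reading, the trial is set up to fail its own hypothesis.

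**Working it through.** **Inputs** (all from the Sample size paragraph, except allocation): 12-week response pc = 0.95; 8-week response pe = 0.90; margin M = 0.05, taken as absolute; one-sided alpha 0.025 (z = 1.960); power 0.90 (z = 1.2816); 1:1 allocation.

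**Formulas** (standard unpooled variance):

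- n per arm = (1.960 + 1.2816)² × [pc(1 − pc) + pe(1 − pe)] / [M − (pc − pe)]², where (1.960 + 1.2816)² ≈ 10.507
- power = Φ{[M − (pc − pe)] / SE − 1.960}, where SE = √{[pc(1 − pc) + pe(1 − pe)] / n}

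**Step 1: the stated inputs.** M − (pc − pe) = 0.05 − (0.95 − 0.90) = 0. The denominator is zero, so no finite n exists. Power = Φ(0 − 1.960) = 2.5%, whatever n is. Simulating the confidence-interval test (1,000,000 runs) gave 2.8% at both 400 and 440 per arm.

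**Step 2: reproduce 400.** With 95% in both arms, pc(1 − pc) + pe(1 − pe) = 0.0475 + 0.0475 = 0.095, and n = 10.507 × 0.095 / 0.05² = 399.3, rounded up to 400. Power at 400: SE = √(0.095/400) = 0.01541, and Φ(0.05/0.01541 − 1.960) = 90.05% (simulated 89.6%).

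**Step 3: other routes to 400.** All at one-sided 2.5% and 90% power:

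| Alternative | n per arm |
|---|---|
| 95% vs 90%, 10-point margin: 10.507 × 0.1375 / 0.05² | 578 |
| 90% in both arms, 5-point margin: 10.507 × 0.18 / 0.05² | 757 |
| Superiority test, 95% vs 90% | 582 (621 with continuity correction) |
| Difference taken with the opposite sign: 10.507 × 0.1375 / 0.10² | 145 |

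For 95% versus 90%, the 10-point margin and the superiority test were also tried at 80% power and at one-sided 5%; none came within 3% of 400. Reading the margin as relative (5% of 95% = 4.75 points) puts the assumed truth just beyond the limit: SE = √(0.1375/400) = 0.01854, and power = Φ(−0.0025/0.01854 − 1.960) = 1.8%.

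**Step 4: what 400 per arm delivers.** With 95% on 12 weeks and a 5-point margin:

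| True 8-week response | M − (pc − pe) | SE | Power |
|---|---|---|---|
| 95% | 0.05 | 0.01541 | 90.1% |
| 94% | 0.04 | 0.01612 | 69.9% |
| 93% | 0.03 | 0.01678 | 43.2% |
| 92% | 0.02 | 0.01740 | 20.9% |
| 90% | 0 | 0.01854 | 2.5% |

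For orientation, the 8-minus-12-week differences in the protocol's Table 2 are 94 − 95 = −1, 96.3 − 96.3 = 0, 95 − 98 = −3, 93 − 95 = −2 and 100 − 98.8 = +1.2 points. True deficits of 1 to 2 points correspond to 70% down to 43% power, and a 3-point deficit to 21%.

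**The case against.** The strongest reply is that the trial is probably sized correctly and only described wrongly. The 90% is exactly 95% minus 5 points, which is the non-inferiority limit. The protocol's background expects near-equality, and every 8-week response in its Table 2 is 93% or higher. Since 400 matches equal 95% rates at the stated margin, alpha and power, the natural reading is that the limit was labelled as an expected rate. The trial would then have about 90% power under equal response, and 2.5% would describe the sentence rather than the trial. This is the likelier explanation, and it makes the repair cheap. It does not make the paragraph right: the 90% is stated as the assumed response in the 8-week arm, and nothing else in the protocol corrects it.

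Two narrower points stand as qualifications. The match to 400 depends on the unpooled formula: a restricted-variance (Farrington–Manning) calculation at 95% in both arms gives about 440 before loss to follow-up. On a one-point grid of rates from 85% to 99%, one other pair came within 3% of 400: 92% on 12 weeks and 93% on 8 weeks (405), which does not use the protocol's 95% reference rate.

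Table 2 is also weak evidence about this regimen. Four of its five two-duration comparisons used sofosbuvir–ledipasvir, and the fifth pools various combinations in children and adolescents. The power figures at 92% to 94% show sensitivity; they do not forecast the result.

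**Conclusion.** The concern holds. As written, the rates and margin are incompatible with both the 90% power and the 400 per arm: they give no finite sample size and 2.5% power at any size. The figure of 400 belongs to a calculation with 95% in both arms. That identification assumes an absolute margin and the unpooled formula. The failure of the stated inputs does not depend on the variance formula, and a relative margin makes it slightly worse. The 90% power is therefore conditional on no loss at all from the shorter course, which the protocol does not say. This must be corrected, because it is the stated basis for the size of the trial and the text does not settle which assumption was used.

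**What to change.** The sponsor should confirm which assumption produced 400 and correct the Sample size paragraph. If it was equal response, state: SVR12 of 95% in both arms, margin of 5 percentage points, one-sided alpha 2.5%, power 90%, 400 evaluable per arm; and name the formula. If 90% was meant as the lowest acceptable 8-week response when the 12-week response is 95%, call it the non-inferiority limit and not the expected rate. A sentence giving the power at true 8-week rates of 94% (70%) and 93% (43%) would be helpful but is optional.

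This costs protocol wording only: no extra patients, and no change to margin, alpha or enrolment. The stated power becomes explicitly conditional on equal response.

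If the sponsor really expects 90% on 8 weeks, the edit above would merely fit the assumption to the number. No sample size gives 90% power at a 5-point margin in that case, and the design itself would have to be reconsidered.

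### The 10% loss allowance is added to 400 rather than divided out, so 440 per arm leaves 396 evaluable, 4 short of the stated requirement (minor)

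*Protocol*

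**What the plan says.** The calculation is in the protocol, in the *Sample size* paragraph under *Flow of the participants*. It gives the number needed before any loss: "The required sample size is estimated as 400 participants in each arm". It then makes the allowance, "Assuming a 10% loss to follow up", and reports the result: "we raised the estimated sample size to 440 participants in each arm and total study size of 880".

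The design inputs come just before. The response rates are introduced with "We assumed the virological response in the reference group (12 weeks) is 95" and "in the experiment group (8 weeks) as 90" (both per cent). The non-inferiority margin is 5%, the power 90%, and the test is set by "level of significance 2.5%, with a one tailed alternative hypothesis". *Detailed research plan* fixes allocation at 1:1. The protocol gives no other loss allowance and no other evaluable target.

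**The concern.** A loss allowance is meant to ensure that the required number remains after the assumed fraction of enrolled participants has dropped out. The fraction therefore applies to the enrolled number, and the required number has to be divided by one minus that fraction. The protocol instead adds 10% of the required number to itself. The enrolled total then falls short of its own target under its own loss assumption.

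What is at stake is consistency more than the trial's conclusion. A reader who applies the stated 10% to the stated 440 does not get back the stated 400. The same step, used on a revised base figure, would carry the error into a new total.

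**Working it through.** **Inputs**, all from the *Sample size* paragraph: required number per arm n = 400; loss d = 10%; enrolled per arm N = 440; total 880.

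**Reproducing the protocol's figure.** n × (1 + d) = 400 × 1.10 = 440 per arm, and 2 × 440 = 880. This matches exactly, so the additive form is what was used.

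**What remains after the assumed loss.** N × (1 − d) = 440 × 0.90 = 396 per arm, or 2 × 396 = 792 in total, against 400 and 800. The shortfall is 4 per arm and 8 in total.

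**The loss that 440 does cover.** 1 − 400/440 = 0.091, that is 9.1%.

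**The enrolled number that a 10% loss needs.** n / (1 − d) = 400/0.90 = 444.4, rounded up to 445 per arm and 890 in total. Check: 444 × 0.90 = 399.6, just short; 445 × 0.90 = 400.5, enough. The difference from the protocol is 5 per arm and 10 in total; 5/440 = 1.1%.

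**Effect on power.** This needs the inputs behind the 400. The usual normal-approximation formula for non-inferiority of two proportions is

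n = (z₀.₉₇₅ + z₀.₉₀)² × [p₁(1 − p₁) + p₂(1 − p₂)] / (margin − assumed difference)².

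- With 95% in both arms and a 5-point margin: (1.960 + 1.282)² × (2 × 0.95 × 0.05) / 0.05² = 399.3, which rounds up to 400.
- With the stated 95% and 90%: margin − difference = 0.05 − 0.05 = 0. No finite n exists, and power is about 2.5% at any size.

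Of the inputs tried, only 95% in both arms gives 400. On those inputs, power = Φ(0.05 / √(2 × 0.95 × 0.05 / n) − 1.960):

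| Evaluable per arm | Power |
| --- | --- |
| 400 | 90.05% |
| 396 | 89.8% |

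The loss is about 0.3 percentage points.

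**The case against.** The strongest case against the point is that it does not matter. A 10% loss rate is a round planning guess, and 9.1% can hardly be told apart from it. The gap is 4 evaluable participants per arm, and no analysis or decision turns on it. The 400 also has to be recalculated because it does not follow from the stated response rates, and 440, 445 and 890 will then all be superseded. This stands as to size and limits the point to a minor correction. It does not remove the error: 440 × 0.90 is 396 whatever the basis of the 400, and a recalculated base inflated in the same way would again fall short.

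Two stronger readings are tempting, and the documents support neither.

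- A reader might infer from *Study end points* that participants who stop the drug for more than two weeks, or who die, are lost on top of the 10%. That list says when a participant's time in the study ends, not who is left out of the analysis. It also contains those who complete follow-up and those with detectable virus after treatment, so it cannot be a list of non-evaluable participants. It puts death and loss to follow-up in one item, so deaths are not shown to fall outside the allowance. Discontinuers may be counted as non-responders and stay in the denominator. The protocol does not say, and analysis sets are commonly left to the statistical analysis plan. No discontinuation rate is given either, so a further reduction cannot be quantified.
- A reader might infer that 445 per arm would secure the stated 90% power. It would do so only with 95% response in both arms, which is not what the protocol assumes.

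**Conclusion.** The point holds as a minor arithmetic error. A requirement of 400, a 10% loss and an enrolment of 440 per arm are mutually inconsistent. The stated loss leaves 396 per arm; 440 covers 9.1%; a 10% loss needs 445 per arm, 890 in total.

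The head counts rest only on the protocol's own three numbers. The power effect of about 0.3 points rests on 95% response in both arms and the normal approximation, and it cannot be stated for the 95% versus 90% that the protocol gives. The error does not threaten the trial. The assumed difference lying on the margin is a separate and far more serious problem in the same paragraph, and correcting the inflation does not resolve it.

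**What to change.** Change one sentence in the *Sample size* paragraph. Either of these keeps the total at 880 and needs no extra patients:

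- state that 440 per arm allows for about 9% loss to follow-up; or
- state that with 10% loss, 440 per arm leaves 396 evaluable per arm.

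If 400 evaluable per arm is to be kept under a 10% loss, the figures become 445 per arm and 890 in total, at a cost of 10 more participants.

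Attach no power figure to this correction: next to the stated 95% and 90% it would be false. When the base number is recalculated on reconciled response rates, divide the result by (1 − loss) and round up.
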